## Methods

### Study design

The effectiveness and fidelity of Houvast are investigated by means of a quasi-experimental research design with two groups and one baseline and two follow-up measurements (Figure 1). Both the intervention group and the control group (‘care as usual’) consist of Dutch services for homeless youth which deliver ambulatory and/or residential care. The services are randomly allocated to the intervention (*n* = 5) or control group (*n* = 5). Stratified randomization is used to ensure that services which deliver ambulant and/or residential care are equally distributed among each group. Randomization of homeless youths was not feasible since entire teams were trained prior to the baseline measurement in the strengths based method. Hence, a quasi-experimental research design is the best feasible design.

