### Data collection

Measurements of primary and secondary outcomes are conducted among youths within the intervention group (*n* = 123) and the control group (*n* = 128) by means of three structured interviews. The first interview (T0) is conducted as soon as possible but within two weeks after the start of ambulant or residential care. Since the average duration of care delivered to homeless youths is three to six months, they are interviewed for a second time (T1) when services end care or when they have received care for a period of six months consecutively. The final follow-up interview (T2) takes place nine months after the first interview. In addition, professionals fill out an electronic questionnaire around T1 to obtain information about their perspective on the working relationship and the quality of life of a particular youth they provide care to. Based on the average number of homeless youths entering the participating services per year, the total period of the data collection is expected to be one year and nine months.

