### Selection and inclusion criteria

Services for homeless youth in the Netherlands who were identified through a web search and through our network were all approached for participation in the study. Inclusion criteria for services to participate in the study were:

1) targeted at delivering ambulant and/or residential care to homeless youth (not specifically at teenage mothers or in general to homeless adults);

2) provision of care to at least 15–20 homeless youths per year;

3) provision of care for an average period of at least three months consecutively (thus excluding emergency shelters).

Of the 35 services that were approached, 18 services attended an introduction meeting about the study. Finally, ten services agreed to participate in the study and eight services declined the opportunity to participate. Reasons for non-participation of services were:

1) not able to generate the necessary financial contribution (the funder requires a financial contribution for services to participate in the study, e.g. to cover expenses for training);

2) already having implemented other working methods;

3) already participating in other studies;

4) pending reorganization within services or organizations.

All youths who enter the service and receive either ambulant or residential care from professionals are included in the study. Exclusion criteria are:

1) youths still living with their parents while receiving ambulant care;

2) youths who end care within two weeks;

3) youths who cannot be interviewed within the first two weeks after entering the service.

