After homeless youths leave the service, locating them for making a second and third interview appointment is challenging because they have often moved to different parts of the country. Therefore, permission is asked in the informed consent at baseline to collect different sources of contact information such as e-mail addresses, phone numbers (e.g. from friends and family) and social media accounts. A protocol for contacting the respondents is established for both follow-up measurements. It consists of the following steps: calling, sending a text message, calling again, calling the contact person of the service, calling again, sending an e-mail, using social media and/or calling friends or family. Youths are excluded if no interview appointment could be made after accomplishing these steps (after four weeks). Every two to four weeks the researcher calls the contact person to verify if participants have left the service (and could be approached for a second or third interview) and to check if their contact information is still up to date.

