In this study several activities were carried out for the implementation of Houvast prior do the start of the data collection. Professionals in the experimental condition received a four day training provided by experienced trainers. Furthermore, two follow-up training days were organized for all trained professionals to further integrate the strengths based principles of Houvast and the fidelity criteria in their working methods, and to mutually exchange experiences about working with the Houvast intervention. In addition, internal coaches at the services within the intervention group were trained in getting familiar with the fundamental elements and competences of coaching to take responsibility for assuring and monitoring the implementation of Houvast and the model fidelity. Team leaders received a two and a half day training to learn what conditions need to be met within the organization in order to successfully implement Houvast. This is of particular importance because for a successful implementation of Houvast the organization and its management must adapt certain perspectives and practices. At the ‘pinnacle’ of the organization are the clients, and all organizational personnel are subservient to them. The managers are subservient to professionals. They need to be well grounded in the strengths based principles which are used by their professionals and to be able to integrate them in their policy [30,31].

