Some limitations may be mentioned as well. First, due to the complex and unpredictable situation of homeless youth, it may be difficult to motivate them to participate in the follow-up interviews. Most youths leave the service within nine months and locating them to make an appointment for a final interview requires a large investment of researchers. By increasing the financial compensation for their time and effort to complete the interviews, they will hopefully remain motivated. Second, even though youths are interviewed for the first time during the first two weeks after entering the service, there is a small possibility that they were influenced in their scoring on the baseline measurement by whether they entered an experimental or a control service. We will inspect the baseline scores of both groups on significant differences in quality of life and the secondary outcomes, the last follow-up measurement will be conducted at nine months after baseline. Even though it is unique to follow homeless youths for this extensive period of time, a longer time span in which their recovery (or not) would have become more apparent would have been ideal. However, due to practical and financial constraints this was not feasible in the present study.

If the Houvast method proves to be effective in improving the quality of life of homeless youths, the study has strong practical relevance as the quality of work within services for homeless youth could be improved and more professionalized.

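### Untraced youths and two-week leavers are excluded after services are allocated; as worded, this loses obtainable follow-up and allows selection that differs by arm

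*Protocol article*

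**What the plan says.** All references are to the Protocol article.

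- Study design: "The services are randomly allocated to the intervention" or control group, five to each. Under Houvast, "several activities were carried out for the implementation of Houvast prior do the start of the data collection". Every exclusion of a youth therefore comes after the service has its arm and, in the Houvast arm, after its staff have been trained.
- Data collection: "The first interview (T0) is conducted as soon as possible but within two weeks after the start of ambulant or residential care". T1 falls at the end of care or after six months of care, and T2 nine months after the first interview. Care lasts three to six months on average.
- Selection and inclusion criteria: the exclusions include "youths who end care within two weeks" and, separately, "youths who cannot be interviewed within the first two weeks after entering the service".
- Procedure: "A protocol for contacting the respondents is established for both follow-up measurements". After the list of contact steps comes the rule "Youths are excluded if no interview appointment could be made after accomplishing these steps (after four weeks".
- Discussion: the difficulty is acknowledged. "Most youths leave the service within nine months and locating them to make an appointment for a final interview requires a large investment".
- Analyses: a two-level multilevel regression (youths within services) is planned. No analysis population is named.

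**The concern.** The tracing rule applies to youths who have consented and given a baseline interview. Because one contact protocol serves both follow-ups and its end point is exclusion, a youth missed at T1 is, on the plain words, out of the study before T2 is due. The wording also leaves open whether the scores already collected stay in the analysis.

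The two-week rule differs in kind, since it is listed as an eligibility criterion. But it depends on behaviour that occurs after a youth has entered an allocated service, and T0 may already have taken place.

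Both events can be affected by the arm. Houvast begins with building a trusting working relationship, and the working relationship is itself an outcome. Tracing also runs partly through the service: its contact person is one of the tracing steps and is called every two to four weeks for updates. If one arm holds on to more of its youths, and those who disappear do worse, a comparison of the remaining youths is biased, and the better-retaining arm is put at a disadvantage.

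**Working it through.** **1. The plan's own attrition figure** (Sample size and power calculation). Inputs: 251 at baseline, 178 at T1, maximum attrition 30%.

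- Implied loss: 251 − 178 = 73, and 73/251 = 29.1%.
- At the full 30%: 251 × 0.30 = 75.3, leaving 175.7 against 178 stated.
- In reverse: 178/0.70 = 254.3 against 251 stated.

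The step reproduces to within 3%. The plan therefore expects about 73 to 75 youths to be lost.

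**2. What the tracing rule does in time.** Suppose care ends at month 3. T1 is then due, and four weeks of failed contact lead to exclusion at about month 4, five months before T2. If T1 is due at month 6, exclusion comes at about month 7, two months before T2. Nothing under Procedure says that T2 is still attempted. A youth missed only at T2 already has T0 and T1 scores, and the rule does not say whether these are kept.

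**3. What the two-week rule adds.** Youths who cannot be interviewed in the first two weeks are already removed by another criterion. So the early-leaver criterion matters for youths who were, or could have been, interviewed and then left. The article does not say how many there are.

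**4. Size, for illustration only.** Let p be the proportion lost in an arm and g the amount by which retained youths score above lost youths. The full mean is (1 − p) × retained + p × lost = retained − p × g, so retained mean = full mean + p × g. With the same g in both arms, a completers-only comparison is biased by

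bias = g × (p₁ − p₀).

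The planned effect of 0.74 and the SD of 1.48 come from the sample size section. The gaps and the losses by arm are assumptions, because the article gives neither.

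| Loss by arm | Gap g | Bias (points) | Share of 0.74 |
|---|---|---|---|
| 35% v 25% | 0.25 SD = 0.37 | 0.037 | 5% |
| 35% v 25% | 0.5 SD = 0.74 | 0.074 | 10% |
| 35% v 25% | 1.0 SD = 1.48 | 0.148 | 20% |
| 40% v 20% | 0.25 to 1.0 SD | 0.074 to 0.296 | 10% to 40% |
| 30% v 30% | same in both arms | 0 | 0% |
| 30% v 30% | differs by 0.25 to 0.5 SD between arms | 0.111 to 0.222 | 15% to 30% |

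The last row is 0.30 × (difference in gap): 0.30 × 0.37 = 0.111 and 0.30 × 0.74 = 0.222.

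**5. What these figures do not measure.** They describe a completers-only comparison. A youth who can never be found has no outcome under any wording. The rule itself costs only the T2 interviews of youths missed at T1 but reachable later, and any partial data that are in fact dropped. Neither number can be derived from the article.

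**The case against.** The strongest reply is that the tracing sentence stands under Procedure, at the end of a list of contact steps. It may say only when attempts stop, or that the youth is out of that one measurement. The sample size section treats such losses as ordinary attrition. The analysis population and the handling of missing data are commonly left to an analysis plan, so their absence here is no fault. This part stands. A reader might infer that the analysis is not intention-to-treat, or that the baseline data of up to 30% of youths are thrown away; the article says neither.

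Other inferences also go too far:

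- That early leavers have often been interviewed before they go. The article sets only an upper limit of two weeks for T0, so this can happen, but its frequency is unknown.
- That the exclusions destroy the balance gained by randomising. Ten services were randomised, youths entered afterwards, and the article calls the design quasi-experimental. The allocation never secured balance between individual youths.
- That all of the roughly 75 expected losses are due to the rule. Most would occur under any wording.

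The plan also works against loss: payments rise from 10 to 20 to 35 euro, several contact sources are collected at baseline, and tracing has many steps. Both rules are identical in the two arms. These measures should reduce loss, but identical rules do not prevent unequal loss when the event that triggers them can depend on the service. Nor do they explain why T2 should be given up after a missed T1, if that is what is meant.

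**Conclusion.** The concern holds as one about stated wording. Followed as written, the tracing rule gives up T2 interviews that may be obtainable and may remove T0 and T1 scores already in hand. The two-week criterion can remove a youth already interviewed at T0. Both depend on events after allocation that the service can influence, so both allow arm-dependent selection. The tracing rule is the stronger of the two, because it concerns enrolled youths with baseline data.

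The size is unknown. The illustrative 0.074 points, 10% of the planned effect, rests on an assumed gap of 0.74 points, an assumed loss of 35% v 25%, and an unadjusted completers-only comparison. It falls to zero if loss and gap are equal in the two arms, and only part of it could be recovered by changing the rule. The point should be corrected because the wording permits an avoidable loss of data and the remedy is cheap, not because a biased analysis has been shown.

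**What to change.** - Under Procedure, replace the exclusion of untraced youths by a statement that they are recorded as missing for that interview, and that T2 is attempted in every youth whatever happened at T1.
- State that every youth with a T0 interview is analysed in the arm allocated to the service, in the planned multilevel model, using all available T0, T1 and T2 scores. With several scores per youth, the model must allow for correlation within youths as well as within services. Add a sensitivity analysis in which the missing scores are not missing at random.
- Do not remove youths already interviewed at T0 because they left care within two weeks. Report early leavers by arm, whether interviewed or not.

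The cost is a change of wording, the added sensitivity analysis, and a few extra contacts under the tracing steps that already exist. Keeping early leavers dilutes exposure to the intervention slightly. Early leavers who were never interviewed stay outside the analysis, and who is interviewed in time depends partly on service staff. Some post-allocation selection therefore remains, and the report by arm would help to show its extent.

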### Houvast

Youths in the experimental group receive care according to the Houvast method. Houvast aims at sustaining the recovery process of homeless youth by focusing on four conditional factors to achieve social quality: social inclusion, socio-economic security, social cohesion and social empowerment [30,38]. A trajectory comprises three parts, i.e., establishing a trusting working relationship and the setting of personal recovery goals based on a strength assessment, activities to support the personal recovery process of homeless youths and to achieve their goals, and evaluation and the ending or continuation of the trajectory. These parts are not free-standing but are interconnected, for instance, building a working relationship with youths and continuously updating the ‘strengths assessment’ and ‘recovery plan’ are important during the whole trajectory, as is constant reflection on activities and achievements. The strengths assessment and personal recovery plan are two primary tools in the strengths model that are meant to be executed in conjunction with each other. The strengths assessment allows youths and professionals to organize and make use of multiple strengths of youths in relation to resources in their living environment. After an estimation of the personal qualities of a particular youth is made, a personal recovery plan can help him or her to achieve their meaningful and important long term recovery goals step by step [30,31].

In this study several activities were carried out for the implementation of Houvast prior do the start of the data collection. Professionals in the experimental condition received a four day training provided by experienced trainers. Furthermore, two follow-up training days were organized for all trained professionals to further integrate the strengths based principles of Houvast and the fidelity criteria in their working methods, and to mutually exchange experiences about working with the Houvast intervention. In addition, internal coaches at the services within the intervention group were trained in getting familiar with the fundamental elements and competences of coaching to take responsibility for assuring and monitoring the implementation of Houvast and the model fidelity. Team leaders received a two and a half day training to learn what conditions need to be met within the organization in order to successfully implement Houvast. This is of particular importance because for a successful implementation of Houvast the organization and its management must adapt certain perspectives and practices. At the ‘pinnacle’ of the organization are the clients, and all organizational personnel are subservient to them. The managers are subservient to professionals. They need to be well grounded in the strengths based principles which are used by their professionals and to be able to integrate them in their policy [30,31].

### Care as usual

Youths in the control group receive care as usual. To get insight into care as usual, professionals fill in a questionnaire about education, years of working experience and the caseload. In addition, the contact person of each service in the control group answers general questions about the average intensity of care, coaching and the actual approach or method used.

### Measures among youths and professionals

#### Demographics

Several demographic characteristics are assessed among homeless youths, including age, gender, nationality, religion, ethnicity, marital status, family composition, residence permit and education. Demographics, such as gender, age, education and years of working experience are also assessed among professionals.

#### Quality of life

The primary outcome is quality of life, measured with the brief version of Lehman Quality of Life Interview [39-41]. This interview measures both objective and subjective quality of life on eight life domains: living situation, daily activities & functioning, family, social relations, finances, work & school, legal & safety issues and health. In addition, the interview contains a global measure of general quality of life which is asked at the beginning and at the end of the interview. The objective quality of life indicators can be categorized as two types: measures of functioning (frequency of social contacts or daily activities) and measures of access to resources and opportunities (income support of housing type). Youths are asked to indicate their subjective satisfaction of quality of life on a seven-point Likert scale, ranging from terrible (1) to delighted (7).

Professionals are asked to rate the quality of life of youth on the aforementioned seven-point Likert scale. For example: “What do you think of the quality of life of the client in general?” The psychometric properties are excellent and comparable to the full interview version [39,40,42].

#### Working relationship

To assess the working relationship between youths and professionals the Psychological Availability and Reliance on Adults (PARA) questionnaire [43] is administered. Both youths and professionals complete their own version of the PARA questionnaire to allow comparison of results. The PARA questionnaire consists of two subscales: perception of psychological availability and reliance. Youths have to answer on a 4-point Likert scale, varying from 1 (disagree) to 4 (agree). The PARA questionnaire was developed primarily for research among institutionalized adolescents [44]. The scale has been used among adolescent athletics as well, where the scale proved to be reliable [45].

### Measures among youths

#### Goals

To gain insight into the main goals homeless youths would like to attain, they are asked during the first interview to report three important personal goals for the next nine months. Next, for every goal a question regarding the importance of the goal and goal self-efficacy is administered which they can both answer on a 4-point Likert scale, varying from 1 (very unimportant or completely disagree) to 4 (very important or completely agree). Goal attainment is evaluated during the second and third interview by asking youths to what extent the earlier reported goals have been achieved. These questions are based on previous research on personal goals in relation to quality of life [46-48].

#### Changes in quality of life

During the second and third interview youths are asked about their possible changes in their quality of life since the last interview. The scale consists of twelve questions with a 7-point Likert scale, ranging from 1 (very much worsened) to 7 (very much improved). An example of a question is: “Has you quality of life been worsened, improved or unchanged compared to previous interview?” The life domains are based on the eight life domains of the Lehman quality of life questionnaire.

#### Substance use

The frequency and intensity of substance use is measured using the Dutch version of the European version of the Addiction Severity Index (EuropASI) [49]. Several questions regarding type of drugs have been added to the questionnaire. The EuropASI has frequently been used in surveys among homeless people with serious mental and/or addiction problems. Studies among substance-abusing populations show satisfactory results for the reliability and validity of the EuropASI [50].

#### Mental and physical health

The Brief Symptom Inventory (BSI-53) [51-53] is used to assess psychological distress. This instrument has widely been used in research among homeless youths and adults to measure mental health [23,54]. The BSI consists of 53 items, covering nine symptom dimensions: somatization, obsession-compulsion, interpersonal sensitivity, depression, anxiety, hostility, phobic anxiety, paranoid ideation and psychoticism. Items are measured on a 5-point Likert scale, ranging from 0 (not at all) to 4 (extremely). The internal consistency and the test-retest reliability are good and were established among a large population of psychiatric patients [53,55].

